## Abstract

**Background:**

Tobacco smoking remains the leading preventable cause of death among American women. Exercise has shown promise as an aid to smoking cessation because it reduces weight gain and weight concerns, improves affect, and reduces nicotine withdrawal symptoms and cigarette craving. Studies have shown that the practice of yoga improves weight control, and reduces perceived stress and negative affect. Yoga practice also includes regulation of breathing and focused attention, both of which may enhance stress reduction and improve mood and well-being and may improve cessation outcomes.

**Methods/Design:**

This pilot efficacy study is designed to examine the rates of cessation among women randomized to either a novel, 8-week Yoga plus Cognitive Behavioral Therapy (CBT) smoking cessation intervention versus a Wellness program plus the same CBT smoking cessation intervention. Outcome measures include 7-day point prevalence abstinence at end of treatment, 3 and 6 months follow up and potential mediating variables (e.g., confidence in quitting smoking, self-efficacy). Other assessments include measures of mindfulness, spirituality, depressive symptoms, anxiety and perceived health (SF-36).

**Discussion:**

Innovative treatments are needed that address barriers to successful smoking cessation among men and women. The design chosen for this study will allow us to explore potential mediators of intervention efficacy so that we may better understand the mechanism(s) by which yoga may act as an effective complementary treatment for smoking cessation. If shown to be effective, yoga can offer an alternative to traditional exercise for reducing negative symptoms that often accompany smoking cessation and predict relapse to smoking among recent quitters.

**Trial Registration:**

ClinicalTrials NCT00492310

## Background

Over 17% of adult women in the United States are current smokers [1]. Tobacco smoking remains the leading preventable cause of death among American women and is a major cause of heart disease, lung and other cancers and many other illnesses [2]. Despite the importance of quitting, smokers encounter a number of significant barriers when they try to quit including nicotine addiction and its associated withdrawal symptoms, cigarette craving, increased negative affect, perceived stress, and post-cessation weight gain [3-6].

Aside from making quitting smoking uncomfortable, these symptoms also increase the individual's risk for relapse to smoking. Perceived stress, negative affect, and the severity of withdrawal symptoms have all been shown to predict time to relapse among recent ex-smokers [5-7]. Post-cessation weight gain and fear of weight gain are common among smokers. They often constitute a substantial barrier to initial cessation and are independent predictors of relapse to smoking, particularly among women [8-11]. Therapies that provide alternative methods to cope with withdrawal symptoms, negative affect, stress and concerns regarding weight gain should improve women's ability to quit and remain quit.

Exercise has been proposed as an aid to smoking cessation for women because of its ability to help offset weight gain during cessation and to reduce *concern *regarding weight gain [12,13]. Because exercise improves affect in adult populations [14-20], exercise may also aid cessation by reducing negative affect and withdrawal symptoms [21,12]. Previous studies have demonstrated that a traditional aerobic exercise program (i.e., brisk walking, bicycling) combined with Cognitive-Behavioral Therapy (CBT) produces higher quit rates among women at post-treatment and six-month follow up compared to CBT without exercise [12,22].

Yoga is an alternative to traditional (western) exercise that has potential as a complementary treatment for smoking cessation. Yoga is comprised of several elements including regulation of breathing, *asanas *(yoga postures), and focused attention (e.g., meditation), all of which may enhance stress reduction and improve mood and well-being [23], which are linked to successful smoking cessation [24]. Several studies have shown that the practice of yoga improves weight control [25-28], and reduces perceived stress and negative affect [29-32]. Based on a synthesis of this evidence-based research, this study is designed to examine the effects of an 8-week yoga program on perceived stress, affect, and the process of quitting smoking among healthy, adult women smokers.

## Methods/Design

### Design

The study design is a randomized, controlled pilot study comparing two conditions: 1) group-based cognitive-behavioral therapy (CBT) for smoking cessation plus a twice-weekly group-based yoga program (***Yoga***); and 2) CBT for smoking cessation plus a group-based wellness program that serves as a contact-control (***Wellness***). Groups of 8-10 individuals enter the program in sequential cohorts and participate in the 8-week treatment program. Assessments take place at baseline (before program entry), end-of-treatment (week 8), and both 3 and 6 months follow up.

### Participant recruitment

Recruitment methods include placing advertisements in local newspapers and websites, posting flyers and placing brochures at commercial locations (e.g., convenience stores, grocery stores) and physician's offices, and television coverage. The study research assistant (RA) is trained to provide information about the program to women who call the program in response to the advertisements, and to screen interested persons for eligibility. Callers are excluded if they smoke less than 5 cigarettes per day, are already physically active (> 3 days of moderate-intensity physical activity or >2 days vigorous intensity exercise per week); are currently practicing yoga, have current heart disease, lung disease, or orthopedic conditions that could make participation in yoga difficult or dangerous; or are currently in treatment for psychiatric illness or are using illegal substances. Eligible participants are also screened to ensure safe participation in physical activity by using the PAR-Q [33], and are sent a letter for their physician to sign giving permission to participate in the program. Individuals deemed eligible following screening are then scheduled for an introductory orientation session during which the study RA presents the details of the study, reviews what is required of participants and administers informed consent. All recruitment procedures and materials including advertisements, consent forms and procedures are approved by the Miriam Hospital Clinical Research Review Board (IRB registration # 0000482).

### Procedures

Enrolled participants are randomly assigned to either the yoga or wellness arms of the study. All participants are also provided on a weekly basis with 1-hour of group based CBT for smoking cessation (separate groups are held for yoga and wellness participants). One yoga and one wellness session per week are scheduled for the same night as the smoking group treatment, so that participants need to travel to the program only two evenings per week.

### Interventions

Yoga classes are conducted twice weekly for eight consecutive weeks by certified yoga instructors with over 15 years experience and who are trained in the *Vinyasa *style. *Vinyasa *is a form of Hatha yoga that emphasizes the continuous flow of movement between postures (*asanas*) and links breath with the movements. In collaboration with the researchers, yoga instructors select a pattern of *asanas *that are appropriate for beginners and teach them consistently during each class. Each class consists of five minutes of breathing exercises (*pranayama*) and seated meditation, followed by 45 minutes of dynamically linked *asanas *(see Figure 1). Classes conclude with ten minutes of closing postures (similar to the "cooling down" period following aerobic exercise) and a final seated meditation.

**Figure 1 F1:**
[figure not shown]
**Basic Vinyasa Yoga Asanas**.

Participants attending the wellness sessions are shown videos regarding a variety of health topics (e.g., low fat diets, breast cancer screenings, back health) followed by a discussion guided by the study RA and distribution of written material relevant to the video topic.

The CBT smoking cessation program is lead by a PhD psychologist with over 10 years experience in conducting smoking cessation groups. Treatment is delivered through use of a program manual to ensure consistent delivery of program content. Topics include self-monitoring, stimulus control, coping with high-risk situations, and stress management for smoking cessation. The program also focuses on topics of concern to women when quitting including: healthy eating, weight management, and balancing multiple roles and multiple demands. This program has been used in our prior studies [12,22]. Participants are also encouraged to select healthy, low-calorie snacks throughout the program and are provided with examples of these snacks to sample. Participants are not provided with nicotine replacement therapy (NRT) or other smoking cessation medications, but are allowed to use them in conjunction with the program, if their primary care physician deems it advisable.

### Measures

Participants complete assessments at baseline, end of treatment (week 8), and both 3 and 6 month follow up (see Table 1). Assessment instruments include surveys of demographic variables, smoking history and nicotine dependence [34] (FTND), Smoking Situations Temptations scale [35](SST), Stage of Change for Smoking Cessation [36], the Smoking Self-efficacy scale [35] (SSE), Withdrawal Symptoms Checklist [37]; and a single item assessing confidence for achieving smoking cessation. Participants also complete the Freiberg Mindfulness Inventory [38] (FMI), and measures of spirituality [39] (STI); [40,41] Anxiety (STAIT); and depressive symptoms [42](CESD-10). Participants also complete assessments of exercise participation [43,44] (PAR), Physical Self-Perception Profile [45] (PSPP); the Short-Form Health Survey [46] (SF-36), and assessments of concern regarding post-cessation weight gain [47] (SSQ).

**Table 1 T1:** Measurement Schedule

Measure	Baseline	weeks 1-8	Post- treatment	Month 3	Month 6
Demographics	✘				
**Smoking Status**					
Smoking History	✘				
Nicotine dependence [34]					
Smoking Behavior, Carbon monoxide	✘	✘	✘	✘	✘
Saliva Cotinine [49]			✘	✘	✘
Withdrawal Symptoms,[37]	✘	✘	✘	✘	✘
**Physical Activity Status**					
7-Day PAR [43,44]	✘		✘	✘	✘
PARQ [33]	✘				
**Weight concerns**					
Weight Concerns [47]	✘		✘	✘	✘
**Psychosocial Measures**					
Self-efficacy, Stage of Change [35,36]	✘		✘	✘	✘
Mindfulness [38]	✘		✘	✘	✘
Spirituality [39]					
Depression [42]	✘		✘	✘	✘
Anxiety [40,41]					
Physical Self-perception [45]	✘		✘	✘	✘
Short form health survey [46]					
Mood (PANAS) [48]		✘			
Cigarette craving					
**Recruitment, Retention and Satisfaction Measures**					
Attendance and drop out		✘	✘		
Group Cohesion			✘		
Consumer Satisfaction			✘		

Each week during the program, participants are assessed for current smoking status (verified by exhaled carbon monoxide [CO]). To assess for acute changes, current positive and negative affect [48] (PANAS), nicotine withdrawal symptoms and cigarette craving are measured once weekly pre- and post-session (yoga or wellness). Smoking outcomes (7-day point prevalence abstinence) are biochemically validated by exhaled carbon monoxide (cutoff < 10 ppm) and saliva cotinine (cutoff = 15 mg/ml)[49].

At the end of each cohort, separate focus groups are to be held for the yoga and wellness participants. Focus groups are conducted by a PhD Psychologist with over 10 years experience in leading focus groups and conducting qualitative research. Focus groups discuss acceptability of the study protocols and intervention components. In particular, discussions explore participant opinions and observations regarding the intervention content, program format, and study design (e.g., program length, timing of sessions, and the number of classes per week). Each of these questions is addressed primarily from the standpoint of the individual participant's experience with the program. A qualitative data collection guide was prepared by the investigators to delineate topics and subtopics to be addressed during the focus group discussions. Each focus group requires approximately 2 hours to be completed, and is audio taped and professionally transcribed for analysis.

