### Planned Analyses

The primary outcome variable is quit status, verified with carbon monoxide (cutoff, 8 ppm) weekly, and with saliva cotinine (cutoff, 15 ng/ml) at the end of treatment, and both 3 and 6 month follow up assessments [49]. To be considered abstinent, subjects need to have a carbon monoxide level less than 8 ppm and a cotinine level less than 57 nmol/L [15 ng/mL].

The primary hypothesis of the study will be tested using a logistic regression to produce an odds ratio measuring the effect of CBT + Yoga on the likelihood of smoking cessation at the post-treatment and follow up assessments. The intention-to-treat principle will be used to calculate treatment effects and differences using all participants initially assigned to treatment. Analyses will also include calculations of the proportion of participants who are continuously abstinent, and abstinent as assessed for 7-day point-prevalence for both treatment groups in order to provide a fuller estimate and understanding of the possible range of the treatment effects. In addition, we will conduct a second longitudinal analysis across time (end of treatment, 3 and 6 month follow up after treatment) using the generalized estimating equations (GEE) approach of Zeger and Liang [51]. This procedure can accommodate covariates and missing data, thus allowing the maximum use of existing data (and thus enhanced power) for detecting treatment effects. This approach is also highly flexible for modeling trend analyses that allow for an alternate way to present intervention effectiveness (comparing trends in both groups over time).

Secondary analyses will examine the effects of yoga on other psychological and behavioral domains including anxiety, quality of life, spirituality, mindfulness and self-esteem. These analyses will consist of a series of repeated measures analyses of covariance using the baseline measure of each variable as a covariate and 3 repeated measurements (end of treatment, 3 and 6 month follow up).

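### The biochemical limits that define abstinence disagree: CO below 10 ppm in one section and below 8 ppm in another, and 57 nmol/L of cotinine is about 10 ng/mL, not 15

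*Protocol article*

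**What the plan says.** The Outcomes section lists the post-treatment cessation rate among the primary outcomes, with feasibility and acceptability. Two sections say how abstinence is verified.

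- **Measures (text after Table 1).** The smoking outcome, 7-day point prevalence, is "biochemically validated by exhaled carbon monoxide (cutoff < 10 ppm) and saliva cotinine (cutoff = 15 mg/ml".
- **Planned Analyses.** Quit status, the primary outcome variable, is "verified with carbon monoxide (cutoff, 8 ppm) weekly, and with saliva cotinine (cutoff, 15 ng/ml" after treatment and at both follow-ups. A subject counts as abstinent only with "a carbon monoxide level less than 8 ppm and a cotinine level less than 57 nmol/L [15 ng/mL".

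Both sections cite reference 49 for their limits. Planned Analyses also reports 7-day point prevalence, which is the outcome that Measures validates at the higher CO limit. Table 1 schedules CO in weeks 1-8 and at every later assessment, but cotinine only after treatment and at months 3 and 6.

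**The concern.** These limits turn a woman's self-report and samples into the yes/no value that enters the logistic regression. If two limits are in print for the same outcome, the classification depends on which sentence, or which unit on the laboratory report, the analyst follows. Choosing after the data are seen would be an unrecorded analytic decision on a primary outcome. The Sample size section gives the main aim as a valid estimate of the effect for planning a larger trial, and that estimate needs a settled case definition.

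**Working it through.** **1. CO.** This needs no outside figure. Measures passes a reading below 10 ppm and Planned Analyses a reading below 8 ppm. Readings from 8 to below 10 ppm pass one rule and fail the other. The article does not say that the limits serve different outcomes, or which one governs.

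**2. Cotinine, mass against molar units.** Planned Analyses treats 57 nmol/L and 15 ng/mL as the same limit. The conversion is

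nmol/L = (ng/mL) × 1000 / molar mass (g/mol).

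The article gives no molar mass. From the formula C10H12N2O it is 10 × 12.011 + 12 × 1.008 + 2 × 14.007 + 15.999 = 176.22 g/mol.

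- The article's own pair would need a molar mass of 15 / 57 × 1000 = 263 g/mol, so it is not reproduced.
- 15 ng/mL: 15 / 176.22 × 1000 = 85.1 nmol/L.
- 57 nmol/L: 57 × 176.22 / 1000 = 10.04 ng/mL.
- With nicotine instead (162.23 g/mol), 15 ng/mL is 92.5 nmol/L and 57 nmol/L is 9.2 ng/mL.
- With 3-hydroxycotinine (192.21 g/mol), the figures are 78.0 nmol/L and 11.0 ng/mL.

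None of these substances makes the two values equal. A result from about 10.0 to below 15 ng/mL passes in mass units and fails in molar units.

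**3. Cotinine, mg/ml against ng/ml.** These differ by a factor of 1,000,000. Planned Analyses gives the same number, 15, twice in nanograms and with the same citation, so mg/ml is read here as a misprint.

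**4. Who changes class.** Both markers must pass, so a band matters only for a woman who reports abstinence and passes the other test. Examples, reading mg/ml as ng/ml (12 ng/mL is 12 / 176.22 × 1000 = 68.1 nmol/L):

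| CO (ppm) | Cotinine (ng/mL) | Measures | Planned Analyses, 15 ng/mL | Planned Analyses, 57 nmol/L |
|---|---|---|---|---|
| 9 | below 10 | abstinent | smoking | smoking |
| below 8 | 12 | abstinent | abstinent | smoking |
| 9 | above 15 | smoking | smoking | smoking |
| 10 or more | 12 | smoking | smoking | smoking |

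The first two women change class and the last two do not. For weekly status no cotinine is scheduled, so the CO limit alone decides among women who report abstinence.

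**5. Size per woman.** The planned total is 60. If arms are about 30 each, one net reclassification moves an arm's quit rate by 1 / 30 = 3.3 percentage points.

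**The case against.** The strongest reply is that Planned Analyses is plainly the working definition. It names the primary outcome variable, states an explicit rule, and gives 15 ng/mL twice against a single molar value that looks like a faulty conversion. On that view the 10 ppm in Measures is a stale figure, and little is at stake in a pilot. Part of this stands: Planned Analyses is the more explicit text and the natural one to keep. But the article never says that it overrides Measures, and its own cotinine limit is inconsistent within one sentence. Nor is this an omission that the full protocol could fill, since the conflicting values are printed here.

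Three stronger readings are tempting, and the article does not support them.

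- **That a literal 15 mg/ml limit would make every smoker abstinent.** It would not, because the CO test must also pass. A vacuous cotinine limit would leave CO as the only biochemical check. In any case the unit is an evident misprint, unlikely to misclassify anyone in practice.
- **That every reading in the two bands changes class.** It does so only when the woman reports abstinence and passes the other marker, where that marker is measured.
- **That three to five reclassified women would equal the whole expected effect.** At 3.3 points each this is 10 to 16.7 points, but only as a worst case with all of them in one arm; changes in both arms offset each other in the difference. The 10%-15% in the Sample size section is called typical of cessation studies. It is not a forecast for this trial, for which the authors say they cannot yet estimate an effect.

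**Conclusion.** The definition of a primary outcome is inconsistent as printed, in two respects that each suffice alone: the CO limit (10 against 8 ppm), and a cotinine limit whose two forms differ by about a third (10 against 15 ng/mL). The mg/ml is a typographical error and adds no weight.

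The CO conflict rests on the article alone. The cotinine point rests on the molar mass from the chemical formula, and it bites only if the molar value is actually applied; the article does not say in which unit results are reported. The number of women in the ambiguous bands cannot be computed from the article, so no bias in a given direction or of a given size is claimed. The figure of 3.3 points per net reclassified woman assumes arms of about 30, which simple randomization does not guarantee.

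**What to change.** Before outcomes are classified, state one abstinence rule and use it in both sections. The shortest route is to keep Planned Analyses and make these corrections:

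- In Measures, change the CO limit to below 8 ppm and the cotinine limit to below 15 ng/mL.
- In Planned Analyses, replace 57 nmol/L with 85 nmol/L, or delete the molar value.
- If 57 nmol/L was the intended limit, state 10 ng/mL throughout instead.

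The sponsor should confirm which cotinine value was meant. Reporting results under the other CO limit as a sensitivity analysis is optional. The cost is a wording correction, with no new data and no change to procedures.

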### Outcomes

The primary outcomes for this study are post-treatment cessation rates, study feasibility and acceptability. Differences in post-treatment (12 week) cessation rates between conditions will provide data for estimates of effect size necessary to calculate power estimates for a major clinical trial. The qualitative and quantitative feasibility and acceptability of the Quitting in Balance program will be assessed by the following outcome measures at the individual participant level:

1. Smoking abstinence rates

2. Accrual and Retention rates

3. Acceptance of Randomization

4. Compliance with study protocol

The feasibility and acceptability outcome measures listed above will be assessed at baseline, 12-weeks (end of treatment), and 3 and 6 months follow-up.

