### Sample size

The nature of this innovative exploratory treatment study necessarily provides limits on the effective sample size, limiting the number of smokers that can be recruited, complete instruments, and participate in the intervention. There is not yet sufficient information to estimate a potential treatment effect size for the CBT + Yoga condition. Thus, our primary interest was to determine a valid estimate of the yoga intervention effect size for smoking cessation for a future, larger efficacy trial. Consequently, we did not conduct power analysis calculations. Rather, the required sample size was based on the number of participants needed to perform valid estimates of the CBT + Yoga intervention smoking cessation rate and possible differential smoking cessation rates between treatments. Given the typical differences in quit rates in most smoking cessation studies, often 10%-15%, [12,22,48,50], we determined that a sample size of 60 participants would be sufficient to obtain initial estimates of effect size with 60% power (medium effect size).

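### The quit-rate difference from about 30 women per arm is too imprecise to serve directly as the effect size for powering the major trial

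*Protocol article*

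**What the plan says.** Outcomes names post-treatment cessation rates, feasibility and acceptability as primary, and says that the between-condition difference in cessation rates "will provide data for estimates of effect size necessary to calculate power estimates for a major clinical trial".

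Sample size makes this the leading purpose: "our primary interest was to determine a valid estimate of the yoga intervention effect size for smoking cessation for a future, larger efficacy trial". It then says "Consequently, we did not conduct power analysis calculations", refers to typical quit-rate differences of 10 to 15 percentage points, and concludes that "a sample size of 60 participants would be sufficient to obtain initial estimates of effect size with 60% power (medium effect size").

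Planned Analyses tests the primary hypothesis by logistic regression on all women assigned. It adds continuous and 7-day point-prevalence abstinence "in order to provide a fuller estimate and understanding of the possible range of the treatment effects". Randomization is simple, between two arms. Neither Outcomes nor Sample size sets a precision target for the difference or mentions a smallest worthwhile difference for the later trial.

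**The concern.** A sample size varies roughly with the inverse square of the difference fed into it, so error in that difference is magnified. A pilot that reads high by chance leads to a major trial that is too small to detect the real effect. One that reads near zero leads to an impractically large trial, and one at or below zero leads to no superiority sample size at all. The article calls the estimate valid and commits it to the next power calculation, so what matters is whether 60 women can support that use. The issue is separate from the 60% power figure: deleting that figure would leave it unchanged.

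**Working it through.** **Inputs from the article.** Total of 60 women; two arms; difference of 10 to 15 points cited as typical; all assigned women analysed.

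**Assumptions.** 30 per arm; Wellness quit rate 5% to 30%; women independent; next trial sized on the observed pilot rates at two-sided 5% and 80% power.

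**The article's own figure.** Reading a medium effect as a standardised difference of 0.5, the normal approximation gives 0.5 × √(30/2) = 1.936.
- One-sided 5%: Φ(1.936 − 1.645) = 61.5%, close to the stated 60%.
- Two-sided 5%: Φ(1.936 − 1.960) = 49%.

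The 60% can therefore be reproduced under one convention, but it does not carry over to the quit-rate differences cited beside it. At two-sided 5%, power with 30 per arm is 12% to 25% for 10 points and 22% to 42% for 15 points.

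**Step 1: precision.** Half-width = 1.96 × √[(p₁(1−p₁) + p₂(1−p₂))/30]. For 20% v 30%: 1.96 × √[(0.16 + 0.21)/30] = 1.96 × 0.111 = 21.8 points.

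For comparison, a margin of ±10 points needs [p₁(1−p₁) + p₂(1−p₂)] × (1.96/0.10)² per arm. That is about 97 to 176 per arm for Wellness rates of 10% to 30%.

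**Step 2: what the next trial would look like.** Per-arm size by the pooled-variance formula, with p̄ the mean of the two rates:

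n = [1.96√(2p̄(1−p̄)) + 0.842√(p₁(1−p₁) + p₂(1−p₂))]² / (p₁ − p₂)².

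Every one of the 31 × 31 possible pilot outcomes was weighted by its binomial probability. Where Yoga was ahead, n was computed at the observed rates, and the real power of that n was then computed at the true rates. The last two columns do not overlap.

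| Wellness rate | True gain | 95% half-width (points) | Correct n per arm | Next trial under 50% real power | Observed difference ≤ 0 |
|---|---|---|---|---|---|
| 5% | 10 | 15.0 | 141 | 27% | 13% |
| 10% | 10 | 17.9 | 199 | 32% | 18% |
| 20% | 10 | 21.8 | 294 | 36% | 23% |
| 30% | 10 | 24.0 | 356 | 36% | 25% |
| 5% | 15 | 16.3 | 76 | 22% | 5% |
| 10% | 15 | 18.9 | 100 | 26% | 8% |
| 20% | 15 | 22.3 | 138 | 29% | 12% |
| 30% | 15 | 24.2 | 163 | 30% | 14% |

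**Worked example.** A pilot reading 20% v 40% gives 82 per arm. If the truth is 20% v 30%, 82 per arm has power Φ[(0.10√82 − 1.200)/0.608] = Φ(−0.48) = 31%.

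**The case against.** **Pilot status.** The study is labelled a pilot, its estimates initial, and Sample size admits that numbers are limited. Feasibility and acceptability are also primary, and accrual, retention, acceptance of randomization and compliance are already collected. This softens the point. It does not remove it, because the same section calls the estimate valid, makes it the primary interest and calls 60 sufficient.

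**The rule is assumed.** The article says that the difference will provide data for an effect size. It does not say that the point estimate will be entered unadjusted or will be the only input. This stands, so the results above are conditional on direct use.

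**Stronger readings to resist.**
- A reader might infer that a zero or negative result would end the program. The article has no stopping rule. It can be said only that such a result gives no usable superiority sample size.
- A reader might add the last two columns and conclude that the plan fails most of the time. The sums run from 27% to 60%. They stay below half in every 15-point case, and the article gives no Wellness rate by which to choose among them.
- A reader might say that the plan ignores sampling error because the only range it mentions is between abstinence definitions. That sentence in Planned Analyses is not offered as sampling uncertainty. Logistic regression and GEE ordinarily yield standard errors, and an article may leave the reporting of intervals to a fuller plan.

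**Consequence.** The problem falls on a later trial and biases no analysis in this one. That is correct and limits its weight.

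**Conclusion.** The concern holds in conditional form. In every scenario examined, the 95% half-width of the pilot difference (15 to 24 points) exceeds the true gain assumed (10 or 15 points). If the observed difference is used directly, the next trial has under 50% real power in 22% to 36% of pilots, and in a further 5% to 25% no superiority sample size can be computed.

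The Wellness rate, alpha, target power and equal arms are assumptions, but imprecision at least as large as the effect holds across the whole range shown. Unequal arms under simple randomization, or positive correlation among women treated in the same group, would reduce precision further.

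The point should be acted on because the article states this use of the data as its primary interest and the remedy is cheap.

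**What to change.** In Outcomes and Sample size, state that the major trial will be powered on a pre-stated smallest worthwhile difference in quit rates, justified on its own grounds, and not on the pilot point estimate. The 10 to 15 points in Sample size are described as typical differences and do not supply that threshold without further argument.

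State that the pilot supplies the Wellness-arm quit rate (with its uncertainty), accrual, retention and acceptability. State also that the between-arm difference, with its 95% confidence interval, will be used only to check whether the worthwhile difference remains plausible. Where Sample size calls the estimate valid, call it preliminary and imprecise. Do not rely on the pilot for within-group correlation: 60 women in cohorts of 8 to 10 make about 6 to 8 cohorts, too few to estimate it well.

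The cost is wording and one confidence interval. Recruitment, treatment and assessments do not change. The pilot gives up the claim to deliver the effect size.
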